### 2.4. Results of classifier development on preliminary data

#### 2.4.1. Variable selection.

We considered 23 variables and eliminated six of them by means of a backwards selection algorithm using Bayesian comparison tests [32], as described in section 2.3. The following 17 variables were selected.

The participant’s age and self-reported sex assigned at birth.The participant’s momentary state of feeling: tired, worried, happy, grouchy, angry, frustrated, worried, unhappy, having experienced a change in mood.Whether the day of the week is Sunday, Monday, Tuesday, Wednesday, Saturday, or SundayWhether the time of day is evening.

We excluded the following variables from the model based on the results of variable selection:

Whether the participant has been hungry, or felt giddy.Day of week: Thursday and Friday.Time of day: morning and afternoon.

#### 2.4.2. Logistic regression.

We determined the optimal number of time lags (1, 2, or 3) to use for logistic regression. The AUC for lag-1 was 0.73, the AUC of lag-2 was 0.78, and the AUC of lag-3 was 0.77. Hence, we selected lag-2 for regularized logistic regression. Detailed results of this analysis are included in S2 Appendix.

The best regularization scheme for logistic regression, as determined using 40-fold cross-validation within the training set, was L2 regularization with C = 0.01. In table 4, we present the model performance for regularized logistic regression, applied to the test examples.

**Table 4 pone.0289235.t004:** Prediction performance of temper outbursts for DMDD, sub-threshold DMDD, and ODD patients in held-out test examples of existing dataset, using regularized logistic regression.

	Precision	Recall	F1-score	Support
No outburst	0.97	0.82	0.89	154
Temper outburst	0.25	0.69	0.37	13

Precision, also called positive predictive value, is defined as the fraction of positive predictions that were true positives (the fraction of times where a temper outburst was endorsed out of the times that the model predicted a temper outburst). Recall, also called sensitivity, is defined as the fraction of positive examples that were predicted to be positive (the fraction of times where the model predicted a temper outburst out of the times in which a temper outburst was endorsed). F1-score is the harmonic mean of precision and recall, given by the formula F1 =  2 *  (precision *  recall)/ (precision +  recall). Support is the total number of test set observations in each category.

Table 5 presents the model weights for logistic regression, as well as Bayesian 95% credible intervals for the variables. We use the Pymc package [35] to implement the Bayesian inference, with N(0,400) prior for the intercept and N(0,0.01) prior (with sigma^2 = 0.01 chosen to match the selected hyperparameter C = 0.01) for each of the non-intercept beta coefficients. For MCMC, we used the NUTS sampler [36] with 10,000 draws and an acceptance target of 0.99.

**Table 5 pone.0289235.t005:** Model weights and intercept for L2-regularized logistic regression, and 95% credible intervals from Bayesian regression.

Variable (lag)	Coefficient	Bayesian 95% credible interval	Variable (lag)	Coefficient	Bayesian 95% credible interval
happy (1)	-0.20	[-0.26, 0.12]	happy (2)	-0.08	[-0.21, 0.18]
unhappy (1)	0.10	[-0.11, 0.27]	unhappy (2)	0.12	[-0.11, 0.27]
grouchy (1)	0.13	[-0.12, 0.27]	grouchy (2)	0.07	[-0.13, 0.25]
frustrated (1)	0.08	[-0.12, 0.27]	frustrated (2)	0.03	[-0.14, 0.25]
angry (1)	0.25	[-0.04, 0.34]	angry (2)	0.22	[-0.05, 0.32]
mood_changed (1)	0.04	[-0.15, 0.24]	mood_changed (2)	-0.01	[-0.16, 0.21]
worried_now (1)	0.11	[-0.12, 0.27]	worried_now (2)	0.11	[-0.11, 0.28]
been_worried (1)	0.08	[-0.13, 0.25]	been_worried (2)	0.09	[-0.12, 0.27]
tired (1)	0.05	[-0.14, 0.24]	tired (2)	0.07	[-0.12, 0.26]
age	-0.08	[-0.20, 0.18]	Monday	-0.11	[-0.23, 0.15]
female	0.17	[-0.05, 0.32]	Tuesday	-0.10	[-0.22, 0.16]
Night	-0.01	[-0.16, 0.21]	Wednesday	-0.01	[-0.19, 0.19]
*(intercept)*	-0.16	[-2.76, -2.03]	Saturday	-0.06	[-0.21, 0.17]
			Sunday	0.02	[-0.17, 0.20]

A positive (negative) value indicates that a YES response is associated with increased (decreased) chance of temper outburst in the next measurement period. Note that the disagreement between the regularized logistic regression intercept and Bayesian interval for the intercept are due to the use of the class balanced cost function for regularized logistic regression. For questions corresponding to labels, please see Table 5.

#### 2.4.3. Random forest.

The best parameters for random forest, as determined by 40-fold cross-validation, were to have an ensemble of 20 estimators, maximum depth of 2, and entropy as the split criterion. The resulting classifier had an AUC of 0.70, which we considered insufficient to warrant continued development of the random forest classifier. Hence, we only plan to evaluate the logistic regression classifier in the planned confirmatory study.

### 2.5. Preliminary data availability

We have made available all data for participants who consented to data sharing at the following link: https://osf.io/4ectb/?view_only=22133bc8b94444a2bb84c553de082268. There were 5 participants who did not consent to having their data shared.

## 3. Confirmatory data collection and analysis protocol

### 3.1. Hypotheses

In an EMA digital platform that queries real-time symptom metrics three times a day [13] and in a model that is shared across participants, we hypothesize that it is possible to prospectively predict a temper outburst in the following assessment based on the following measurements:

The participant’s age and self-reported sex assigned at birth.The participant’s momentary state of feeling: tired, worried, happy, angry, frustrated, having been worried, unhappy, having experienced a change in mood.Whether the day of the week is Monday, Tuesday, Wednesday, Thursday/Friday, Saturday, or Sunday. *Remark*: the reason why Thursday and Friday are considered as one category is because those two variables were eliminated as an outcome of feature selection on preliminary data (see section 2.4.1). Hence, any observation which does not have the indicator 1 for any of the remaining days (Monday, Tuesday, Wednesday, Saturday, Sunday) can be considered in the “left-out” group which consists of all observations occurring on Thursday or Friday.Whether the time of day is evening, or before evening (morning and afternoon being considered as one category). *Remark*: the reason why morning and afternoon are considered as one category is because those two variables were eliminated as an outcome of feature selection on preliminary data (See above Remark).

### 3.2. Design plan

#### 3.2.1. Study design.

*Study Type.* The study is an observational study, since data is collected from study participants that are not randomly assigned to a treatment.

*Blinding.* No blinding is involved in this study. The authors had access to information that could identify participants during and after collection of data.

*Study design.* The preliminary data were collected according to a protocol from [13]. No participants were treated during the data collection. Quoting from [13]:

“Youth participants enriched for symptoms of irritability and temper outbursts and an identified parent completed a clinical evaluation visit before being enrolled in the research protocol. Participants subsequently completed a standardized EMA training session during which a research assistant familiarized the participant with the smartphone and protocol and reviewed each EMA item by guiding the participant through a practice prompt. To enhance feasibility and compliance, for each day during the upcoming 7 days of EMA, participants preselected 60-min periods during standardized time windows within which prompts would be delivered: morning/before school (6:00–9:00 a.m.), afternoon/after school (3:00–6:00 p.m.), and evening/before bedtime (7:00–10:00 p.m.). The actual prompt times were randomized within these time periods... Participants used either a personal or a study- provided smartphone...

Following the training session, participants were prompted three times per day for seven consecutive days. At each prompt, participants received a text message with a link to the website through which the items were delivered. Once the prompt was received, participants had 60 min to complete the assessment before it expired and was considered incomplete.“

#### 3.2.2. Data collection procedures.

Recruitment will focus on youth aged 8–18 years meeting criteria for DMDD, sub-threshold DMDD, or ODD.

The means of planned recruitment and exclusion criteria will be identical to the procedures described in [13], as quoted:

“Participants were recruited via direct mailings and online advertisements. Participants were evaluated for eligibility and diagnostic status by a doctoral- or master’s-level clinician using the Schedule for Affective Disorders and Schizophrenia for School-Age Children – Present and Lifetime version [37]. Primary diagnosis was based on the chief presenting complaint and clinician judgment of the most severely impairing diagnosis. Recruitment focused on youth whose irritability was chronic and not clearly related to another ongoing or episodic diagnosis (e.g., major depressive disorder, bipolar disorder). Exclusion criteria were: IQ < 70, assessed using the Wechsler Abbreviated Intelligence Scale [38]; a diagnosis of posttraumatic stress disorder, schizophrenia, neurological disorder, developmental disorder, bipolar disorder, or obsessive–compulsive disorder; a current major depressive episode; or substance abuse within 3 months of participation. Participants and their parents provided written assent and consent, respectively. Participants were compensated and offered a monetary bonus for completing ≥75% of prompts. The study was approved by the National Institute of Mental Health Institutional Review Board.”

A second wave of data collection, for the confirmatory set, is currently ongoing at NIMH.

#### 3.2.3. Sample size.

In the confirmatory data set (to be completed by approximately 2027), we plan to collect 20 participants, with an expected total of 300.79 prompts. We determined this prospective sample size based on a power analysis with simulated data.

We simulated data based on a simulation ground truth logistic regression model with L2 penalization, and penalization constant tuned to produce data that would result in a cross-validated accuracy of around 0.40, matching what we saw in the real data. Then, by resampling without replacement participants from the training set, and drawing labels according to the predictions of the simulation ground truth model, we produced synthetic datasets with sample sizes ranging from 1 to 34 participants. For each target sample size, we drew 1000 synthetic data sets of that size, and we assessed the power in terms of the average proportion of coefficients with incorrectly estimated signs using regularized balanced logistic regression. Detailed results are presented in S1 Appendix.

Based on the results of the power analysis, there was a consensus that, when taking into account both the clinical and methodological considerations, the more conservative would be 25 participants, even though a case could be made to justify 15 participants. Our consensus decision is to take the average of these two extremes, and therefore our new plan is to stop collecting participants for this analysis once we have collected 20 participants, which results in around 300.79 prompts on average and has a 31% average sign error for estimating coefficients (Table in S1 Appendix). For this number of prompts, assuming the same proportion of prompts will contain outbursts as in the exploratory sample (10%), we expect to see 30.08 temper outbursts on average.

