### 3.3. Statistical models

#### 3.3.1. Data.

The full list of selected variables is as follows

Response variable: Temper outburst (binary)

Predictor variables:

non-time-varying:Demographic variables: age and self-reported sex assigned at birth.time-varying:Indicator variables from previous time point: giddy, tired, worried, happy, grouchy, angry, frustrated, worried, unhappy, change in mood.Time of day and day of week. See section 2.2.1, “Measured Variables” for details.

While we used data-splitting for model development in the analysis of the preliminary data, in the confirmatory dataset we will use the entire confirmatory dataset as a test set to evaluate the logistic regression classifier we have already developed.

**Transformations.** The day of week will be extracted from the timestamp of the raw data.

Recall that the data will be collected for 7 days, 3 times a day per observation period, with some participants completing multiple observation periods (details in sampling plan). The time of day will be obtained from the column number of the raw data (as columns 1-21 are the 21 consecutive EMA prompt periods, with morning, afternoon, and evening for each of 7 days). The participant’s age will be rounded to integer values.

All predictors will be rescaled to lie between 0 and 1 using min-max scaling. Observations with missing entries will be excluded from the analysis. Since we do not use observations with partial entries, we will report the missing cases on an observation-by-observation basis rather than a variable-by-variable basis.

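### The sample size of 20 is justified by sign errors of refitted coefficients, but the confirmatory analysis only scores a frozen classifier; the simulation's accuracy of 0.40 is also unexplained

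*Protocol article*

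**What the plan says.** Section 3.2.3 of the protocol article states that "we plan to collect 20 participants, with an expected total of 300.79 prompts" and that the number came from a simulation-based power analysis. The criterion is explicit: "we assessed the power in terms of the average proportion of coefficients with incorrectly estimated signs", using regularized balanced logistic regression on each synthetic data set. At 20 participants the design "has a 31% average sign error for estimating coefficients". The number 20 is the midpoint of 15 and 25: "Our consensus decision is to take the average of these two extremes". The simulation's ground truth was tuned to a "cross-validated accuracy of around 0.40, matching what we saw in the real data". With a 10% outburst rate, "we expect to see 30.08 temper outbursts on average".

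The confirmatory analysis is described in Sections 3.3.1 to 3.3.3. Section 3.3.1 says that "we will use the entire confirmatory dataset as a test set to evaluate the logistic regression classifier we have already developed". Section 3.3.2 names one pre-fitted model. Section 3.3.3 defines the inference as 95% Beta credible intervals for precision and recall under a Jeffreys prior. It expects the precision interval to lie within 0.1 to 0.4 and the recall interval within 0.55 to 0.95.

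Table 4 (Section 2.4.2) gives the held-out performance of the classifier. For 154 non-outbursts, precision is 0.97, recall 0.82 and F1 0.89. For 13 outbursts, precision is 0.25, recall 0.69 and F1 0.37.

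**The concern.** There are two separate problems in the paragraph that fixes the sample size.

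First, the power criterion belongs to a different analysis. The sign error describes how well a model refitted to 20 participants would recover coefficient directions. No confirmatory step fits coefficients or draws a conclusion about a sign. How precisely a frozen classifier's recall is estimated depends mainly on the number of outbursts. For precision it depends on the number of predicted outbursts. The 31% figure speaks to neither.

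Second, the simulation is said to be calibrated to the real data through an accuracy of about 0.40, but the article reports no accuracy near that value. With outbursts at roughly one prompt in ten, an accuracy of 0.40 would be far worse than never predicting an outburst.

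At stake is whether a reader can tell what 20 participants will show about precision and recall, and whether the expected results in Section 3.3.3 are attainable at that size.

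**Working it through.** **1. The plan's own sample-size arithmetic reproduces.** (15 + 25)/2 = 20, and 0.10 × 300.79 = 30.08 outbursts. The 31% sign error cannot be checked, because it comes from S1 Appendix, which is not shown.

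**2. Accuracy implied by Table 4.** I searched all 2×2 tables with 13 outbursts and 154 non-outbursts. Only one agrees with all six rounded figures: TP 9, FP 27, FN 4, TN 127.

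| Metric | Calculation | Value |
|---|---|---|
| Accuracy | (9 + 127)/167 | 0.81 |
| Accuracy of always predicting no outburst | 154/167 | 0.92 |
| Balanced accuracy | (9/13 + 127/154)/2 | 0.76 |
| Outburst F1 | 2 × 9/(2 × 9 + 27 + 4) | 0.37 |
| Outburst F2 | 5 × 9/(5 × 9 + 4 × 4 + 27) | 0.51 |

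The stated 0.40 does not reproduce as an accuracy. At a 10% outburst rate and recall 0.69, an accuracy of 0.40 would require a specificity of (0.40 − 0.10 × 0.69)/0.90 = 0.37, against 0.82 in Table 4.

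**3. What the planned size gives for recall.** The interval is the 2.5% and 97.5% quantiles of Beta(TP + 0.5, FN + 0.5), with prompts taken as independent.

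- 30 outbursts (the plan's 10% rate): 21 hits, the most likely result if recall is 9/13, give [0.52, 0.84], width 0.32.
- 23 outbursts (Table 4's rate, 300.79 × 13/167 = 23.4): 16 hits give [0.49, 0.85], width 0.36.

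**4. What it gives for precision.** The interval uses Beta(TP + 0.5, FP + 0.5). The width depends on how many positives are predicted.

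- 21 hits at the plan's precision of 0.25 means 21/0.25 = 84 predicted positives (63 false). The interval is [0.17, 0.35], width 0.18.
- Table 4's outburst rate, recall and specificity over 301 prompts give about 16.2 true and 48.7 false positives. The interval is [0.16, 0.36], width 0.21.
- A 10% outburst rate with Table 4's recall and specificity gives about 20.8 true and 47.5 false positives, so a precision of 0.30. The interval is [0.21, 0.42], width 0.21, and its upper limit passes the expected 0.4.

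**5. Probability of meeting the plan's recall expectation (interval inside 0.55 to 0.95), with true recall 9/13.**

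- With 30 outbursts, only 22 to 25 hits qualify. 21 hits put the lower limit at 0.52; 26 put the upper limit at 0.953. The binomial probabilities sum to 0.144 + 0.113 + 0.074 + 0.040 = 0.37.
- With 23 outbursts, only 18 or 19 hits qualify: 0.124 + 0.073 = 0.20.

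Prompts are clustered within participants. Section 2.2 reports participant-level outburst frequencies from 0 to 0.73, with SD 0.16 around a mean of 0.10. Clustering would probably lower these probabilities. The documents give no within-participant correlation of correct predictions, so the amount cannot be computed.

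**The case against.** Several points on the other side have force.

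- **Cross-validated versus held-out.** A reader might infer that Table 4 directly contradicts the 0.40. It does not quite: Section 3.2.3 speaks of cross-validated accuracy, and Table 4 is a single held-out set with 13 outbursts. The two need not agree, and S1 Appendix may name the metric. What stands is that the gap from 0.40 to 0.81 is too wide to be plausible for the same metric. A mislabelled F-score is possible, since the outburst F1 is 0.37, but that is an inference.
- **Interval expectations are stated.** It would be wrong to say that the plan ignores interval precision. Section 3.3.3 gives expected limits, Section 3.3.4 triggers diagnostics at widths above 0.5, and Section 3.2.3 gives the expected outburst count. What is missing is any link between these and 20 participants.
- **Some coefficients are updated.** Section 3.3.4 plans exploratory fine-tuning on individual test participants, and the diagnostic refits use the training set. So it is only the confirmatory analysis that refits nothing. Both exploratory steps are judged on predictive performance, not on signs, and do not rescue the criterion.
- **Does 20 become wrong?** A reader might infer that enrolment must rise. The documents do not support that. The limits in Section 3.3.3 are expected results, not a success rule, and the plan sets no required interval width.

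**Conclusion.** The concern holds. The stated justification for 20 participants does not apply to the confirmatory question, and the calibration figure of 0.40 is unexplained and implausible as an accuracy. The consequence is visible on the plan's own terms: a classifier performing exactly as in Table 4 would more likely than not miss the stated recall expectation (probability of meeting it about 0.37 at 30 outbursts, 0.20 at 23). These figures assume independent prompts, true recall of 9/13 and the plan's Beta formula. The value 9/13 is itself uncertain: its Jeffreys interval is about 0.42 to 0.89. The analysis remains computable and valid as description. The defect lies in the rationale and in the expectation attached to it, so this should be corrected but does not block the study.

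**What to change.** 1. In Section 3.2.3, name the metric that was about 0.40. If it really was accuracy, re-tune the simulation so that it reflects the observed performance.
2. Replace the sign error as the basis for the sample size with the expected widths of the precision and recall intervals at 20 participants. State the assumed recall, specificity, outburst rate (about 8% to 10%) and within-participant correlation, each as a range. The sign-error table can stay in S1 Appendix as background.
3. Do not obtain those widths by scoring the frozen classifier on resampled training participants: it was fitted to them and the result would be optimistic. The held-out set has only 11 participants, so simulation under stated assumptions is the practical route.
4. Restate the recall expectation in Section 3.3.3 so that it agrees with what 20 participants deliver, and check the precision expectation against the assumed outburst rate.

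Enrolment need not change. The cost is a modest new simulation, rewritten text in Sections 3.2.3 and 3.3.3, and a less favourable but relevant stated expectation. Section 3.2.2 says confirmatory collection is under way, so the change should be made before results are seen.

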### 3.3. Statistical models

#### 3.3.1. Data.

The full list of selected variables is as follows

Response variable: Temper outburst (binary)

Predictor variables:

non-time-varying:Demographic variables: age and self-reported sex assigned at birth.time-varying:Indicator variables from previous time point: giddy, tired, worried, happy, grouchy, angry, frustrated, worried, unhappy, change in mood.Time of day and day of week. See section 2.2.1, “Measured Variables” for details.

While we used data-splitting for model development in the analysis of the preliminary data, in the confirmatory dataset we will use the entire confirmatory dataset as a test set to evaluate the logistic regression classifier we have already developed.

**Transformations.** The day of week will be extracted from the timestamp of the raw data.

Recall that the data will be collected for 7 days, 3 times a day per observation period, with some participants completing multiple observation periods (details in sampling plan). The time of day will be obtained from the column number of the raw data (as columns 1-21 are the 21 consecutive EMA prompt periods, with morning, afternoon, and evening for each of 7 days). The participant’s age will be rounded to integer values.

All predictors will be rescaled to lie between 0 and 1 using min-max scaling. Observations with missing entries will be excluded from the analysis. Since we do not use observations with partial entries, we will report the missing cases on an observation-by-observation basis rather than a variable-by-variable basis.

#### 3.3.2. Analytic approach.

We will evaluate one pre-fitted model, L2-regularized logistic regression, as developed in section 3.

We will use the “lag-2” model as described in section 2.3. Hence, time-varying predictors will be included with both lags of 1 and 2, so that information in the two measurement periods proceeding a temper outburst is used to predict the absence/presence of a temper outburst. All variables will be scaled with min-max scaling to lie between 0 and 1.

